#### Secondary outcomes: explosive power, aerobic capacity, and tendon CSA and length

The explosive power will be measured by using vertical jump test. The test is often used as a measurement of lower-body power [44] and thus as an indirect measure of performance. Vertical jump testing has been shown to be a valid and reliable measure of lower-body explosive power [44].

The high-intensity aerobic capacity will be measured by the YYIR tests. The test is a simple method for examining an athlete’s capacity to perform a repetitive high-intensity aerobic exercise [9]. Yo-Yo test has been repeatedly proven as reliable (ICC = 0.86 to 0.95) [49], and also, YYIR1 has been proven as a valid and reliable tool with high reproducibility for measuring high-intensity aerobic capacity from various sports and competition levels [16, 27], and a moderately reliable predictor of VO2 max [44, 49].

Tendon CSA and length will be measured using ultrasound imaging (Esaote, Technos MPX) in B-mode with a 10-MHz linear array transducer the same as muscle architecture measurements.

The muscle architecture and PT length measurements will take place from 1 March 2020 until 10 March 2020 for both groups in Tishreen University Hospital (Radiology Department). After that, the measurements of torque, power, and work will take place until 16 March 2020 in Tishreen University Hospital (Physical Therapy Department). Explosive power and aerobic capacity measurements will start directly after that until 20 March 2020 at Latakia Sports City Stadium.

### Participant timeline {13}

Participants will be assessed according to their medical reports from 1 February 2020. After meeting all the eligibility for recruitment, we will make appointments for the pre-tests in the next 20 days. The training program will take place from 15 April 2020 (Fig. 1).

**Fig. 1 Fig1:**
[figure not shown]
Participant timeline and study design

### The schedule of enrolment, interventions, and assessments

Table 4 shows the schedule.

**Table 4 Tab4:** The schedule of enrolment, interventions, and assessments

Post-allocation study period (weeks)															
	Enrolment	Baseline	Post-allocation												Follow-up
Timepoint**	***2 weeks***	0	***1***	***2***	***3***	***4***	***5***	***6***	***7***	***8***	***9***	***10***	***11***	***12***	
**Enrolment**															
**Eligibility screen**	X														
**Informed consent**	X														
**Allocation**		X													
**Interventions**															
***Football group***			X	X	X	X	X	X	X	X	X	X	X	X	
***Aerobic group***			X	X	X	X	X	X	X	X	X	X	X	X	
**Assessments**															
***VO2 max, explosive power***		X													X
***Range of motion, muscular power, and work***		X													X
***Muscle architecture (CSA, FL, MT, PA) and PT length***		X													X

### Sample size {14}

The sample size was calculated by using “Gpower” software 3.1.9.2. For the determination of the effect size, we made a pilot study which included 10 participants from every single group. We measured the PA of VM for both groups. The mean (M) for football group was 10.59 and 8.17 for AG. Also, the standard deviation (SD) for FG was 2.80 and 2.01 for aerobic one. Based on this, the effect size was 0.992. The α level was 0.05, and the power was 0.95. The minimum numbers of sample were 46 participants.

We raise the sample to 60 for better result. Sixty untrained but healthy adult men are equally divided into two groups (mean ± SD age 55 ± 5). This sample includes a dropout of 15% and provides a moderately detectable change between a group with an alpha level of *p* < 0.05. Some of them had experienced some of the age-related neuromuscular problems or diseases, at least within the last year.

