## Abstract

**Background:**

Sports and exercise training can attenuate age-related declines in physical function. As people age, they suffer a progressive deterioration of overall muscle structure and function, such as muscle diameter, strength, mass, and power. Therefore, supporting older adults—aged 50 years and above—to continue being physically active is a very important factor. Several forms of exercise (strength, agility, endurance, balance, and flexibility) are recommended. In this regard, football has been repeatedly shown to be an integrative approach to promote measures of strength, endurance, and agility. However, there has been no previous randomized controlled trial that comparatively investigates the effects of football training versus traditional aerobic exercise training on muscle architecture and patella tendon properties in healthy community dwellers. The study protocol is designed to examine whether football differentially affects muscle thickness, muscle length, fascicle length, pennation angle, patella tendon length, and thickness compared to a workload matched traditional aerobic exercise training regimen.

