Recreational football can be an alternative exercise modality for untrained, healthy, or unhealthy middle-aged and older adults [22]. Football is an effective stimulant of musculoskeletal, metabolic, and cardiovascular adaptations of importance for health and thereby reduces the risk of developing lifestyle diseases [22]. Also, it has effects on various age categories and populations on muscular fitness, health profile, and physical capacity [29]. In this context, aerobic activity is efficient to improve physical fitness and functionality in adults. In fact, maintaining a healthy life would be more appropriate in step-aerobics exercises due to having higher tempos and rhythms than the run-walk exercises [35]. Moreover, aerobic program training can enhance muscle protein, synthesis, irrespective of age [21].

Several studies have recently focused on the effect of resistance or strength training programs on muscle architecture. There are no previous studies that have analyzed the effects of football training program or aerobic training program on muscle architecture, nor there is comparative study between football and aerobic training methods in terms of their effectiveness on muscle architecture. The study protocol is designed to investigate whether football differentially affects muscle architecture, work, power, torque, and patella tendon (PT) compared to traditional aerobic exercise training program in adult men.

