## Statistical methods

### Statistical methods for primary and secondary outcomes {20a}

We will use the SPSS V20 for statistical data analysis. First of all, we will calculate “mean separation” as a comparison for every means. The objective is to identify where and how many differences exist. Normality tests (SPSS Explore) will be used to determine if the data is well modeled by a normal distribution, and to compute how likely it is for a random variable. Paired samples *t* test will be used to compare the mean of every group to measure the effects of every single training method. Independent samples *t* test will be used to compare the mean between the football and aerobic groups before and after the intervention.

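### The minimum of 46 participants reproduces only with a one-sided t test, but no one-sided test is declared; two-sided, 95% power needs 56

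*Protocol article*

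**What the plan says.** Under Sample size {14}, the protocol article reports a pilot of 10 men per group on the pennation angle of the vastus medialis. The pilot results are "The mean (M) for football group was 10.59 and 8.17 for AG", and "the standard deviation (SD) for FG was 2.80 and 2.01 for aerobic one". From these: "Based on this, the effect size was 0.992". The remaining inputs are "The α level was 0.05, and the power was 0.95", entered in G*Power 3.1.9.2, and the result is "The minimum numbers of sample were 46 participants". The section then raises the number to 60 and says that this figure includes 15% dropout. It does not say whether alpha is one-sided or two-sided.

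The comparison is framed without a direction. The abstract states: "The study protocol is designed to examine whether football differentially affects muscle thickness". The Background and rationale {6a} repeats the aim "to investigate whether football differentially affects muscle architecture" and also asks which of the two programmes is better. Under Statistical methods {20a}, an independent-samples t test "will be used to compare the mean between the football and aerobic groups before and after the intervention", again with no direction given.

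**The concern.** A comparison that could favour either programme, analysed with a standard t test at 0.05, is normally taken as two-sided. Under that reading three printed figures, alpha 0.05, power 0.95 and a minimum of 46, cannot all be right. This is the only power justification in the article. A reader who relies on it would believe that 46 evaluable men secure 95% power for the planned comparison, when they secure less. The figure of 46 also sets how far the planned 60 appears to exceed the minimum, and so how much attrition the trial seems able to absorb.

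**Working it through.** **Inputs** (all from Sample size {14}, except the 1:1 allocation from Concealment mechanism {16b}): means 10.59 and 8.17; SDs 2.80 and 2.01; alpha 0.05; power 0.95; stated d = 0.992; stated minimum 46; planned 60; dropout 15%.

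**Effect size.** Pooled SD = √[(2.80² + 2.01²)/2] = 2.437. The difference is 10.59 − 8.17 = 2.42, so d = 2.42/2.437 = 0.993. This agrees with the stated 0.992, and either value leads to the same sample sizes. The stated 0.992 is used below.

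**Method.** Exact power of the two-sample t test from the noncentral t distribution, with df = n₁ + n₂ − 2 and noncentrality d·√[n₁n₂/(n₁ + n₂)]. The critical value is the 0.95 quantile of t for one-sided alpha 0.05 and the 0.975 quantile for two-sided.

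**Reproducing 46.** With 23 per arm, df = 44 and the noncentrality is 0.992 × √11.5 = 3.364.

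| Per arm | Total | One-sided power | Two-sided power |
|---|---|---|---|
| 22 | 44 | 0.944 | 0.895 |
| 23 | 46 | 0.952 | 0.908 |
| 27 | 54 | 0.975 | 0.947 |
| 28 | 56 | 0.978 | 0.954 |
| 30 | 60 | 0.984 | 0.965 |

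One-sided, 22 per arm falls short of 0.95 and 23 reaches it, so the minimum is exactly 46. Two-sided, 27 per arm falls short and 28 reaches it, so the minimum is 56. That is 10 men more than stated (10/46 = 22%). The normal approximation gives 22 per arm one-sided and 27 per arm two-sided, so it does not give 46 either way.

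**Planned sample.** With 60 men and no dropout, two-sided power is 0.965. With 15% dropout, 60 × 0.85 = 51 remain. Split 25 and 26, the noncentrality is 0.992 × √(650/51) = 3.54 with df = 49, and two-sided power is 0.935.

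**Enrolment at 15% dropout.** To keep 46 evaluable: 46/0.85 = 54.1, so 55. To keep 56 evaluable: 56/0.85 = 65.9, so 66. The planned 60 lies between the two.

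**The case against.** The strongest reply is that the trial does not randomise 46 men. It randomises 60, and two-sided power at 60 exceeds the stated 95%. Power falls to about 91% only if 14 of 60 are lost (23%), which is more than the 15% assumed. This stands, and it limits the point to a correction of the stated justification.

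Second, the one-sided setting is inferred from the reproduction; the article does not state it. A two-sided calculation at 90% power also gives 46, so the misprint could be in the power. This stands as a caveat, but the article prints 0.95, and on either explanation one printed item needs correcting.

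Third, the Discussion argues that football is the broader muscular stimulus, which leans towards football. It still words the primary hypothesis as differences between the groups and declares no directional test, so it does not support a one-sided alpha.

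A reader might also infer that 15% was added to too small a base, or that 60 is offered as a generous surplus over 46. The documents support neither. The section does not derive 60 by inflating 46 (that would give 55) and does not describe the margin in such terms.

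**Conclusion.** The stated minimum does not match the planned comparison. At the article's own inputs, 46 with 95% power holds only one-sided; two-sided the minimum is 56, and 46 men give about 91%. The correction is worth making but is not critical. For d = 0.992, two-sided power is 96.5% with 60 evaluable men and about 93.5% with 51, the latter roughly 1.5 points below target. It would be wrong to infer from this point that the trial is seriously underpowered or needs more men.

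The conclusion assumes a two-sided test, which the article implies but does not state, equal allocation, and the pilot effect of 0.992. It does not endorse that effect size. The sample size section and the Discussion both speak of a moderate difference; if that meant d = 0.5 (an assumption, as the article gives no figure), two-sided power with 60 men would be about 0.48.

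**What to change.** In Sample size {14}, state that alpha 0.05 is two-sided and give 56 men (28 per arm) as the minimum for 95% power at d = 0.992; alternatively keep 46 and state its power as about 91%. Add that 60 randomised with 15% dropout leaves 51 evaluable and about 93% two-sided power at that effect size. In Statistical methods {20a}, state that the between-group t test is two-sided at 0.05.

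Declaring a one-sided test would also make 46 consistent, but it would conflict with the non-directional objective and would need its own justification.

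The cost is wording only, and the stated power becomes slightly less favourable. Recruitment, procedures and the planned test are unchanged, and no extra participants are needed. Holding the full 95% after 15% dropout would take 66 enrolled, but a shortfall of about 1.5 points does not call for that.

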However, so far, almost no studies compared the effects of football and running training interventions on the age-related decline of muscle strength and structure. This is the first study that aims at investigating the differential effects of football and running training response on muscle architecture, patella tendon properties, and thigh muscles. The proposed study should benefit participants’ physical, psychological, and social dimensions. It is assumed that running and football training not only may result in the improvement of the aerobic capacity and systemic arterial blood pressure reductions, but also can improve the functional parameters, including increased explosive power strength, balance, agility, and functional capacity. As our primary hypothesis, we expect moderate differences between both groups in muscle architecture CSA, FL, MT, PA, knee ROM, passive resistive torque, work, power, and tendon length and thickness as football entails are broader and multimodal muscular stimulus compared to aerobic training alone. These may lead to overall decrease in obesity risk and stress, and it could also prevent heart diseases, maintain muscle mass, and reduce the risk of depression. Moreover, the training programs may enhance muscle architecture and tendon thickness that causes a perceptible decrease in the probability of dynapenia and sarcopenia in the future.

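### The trial is sized on a difference of about one SD, yet it describes its sensitivity and its primary hypothesis as moderate; at an assumed 0.5 SD, power with 51 completers is about 42% two-sided or 55% one-sided

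*Protocol article*

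**What the plan says.** The section Sample size {14} describes the source of the planning effect: "we made a pilot study which included 10 participants from every single group". The outcome was the pennation angle of the VM. It reports that "The mean (M) for football group was 10.59 and 8.17 for AG" and that "the standard deviation (SD) for FG was 2.80 and 2.01 for aerobic one". It continues: "Based on this, the effect size was 0.992". The error rates follow: "The α level was 0.05, and the power was 0.95". The result is given as "The minimum numbers of sample were 46 participants". Whether the test is one-sided or two-sided is not stated.

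The section then raises the sample to 60, says that this includes 15% dropout, and says that the sample "provides a moderately detectable change between a group with an alpha level of" 0.05. No effect size is attached to that phrase.

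The Discussion states the hypothesis: "As our primary hypothesis, we expect moderate differences between both groups in muscle architecture CSA, FL, MT, PA", and extends it to range of motion, torque, work, power and tendon measures. The section Statistical methods {20a} plans an independent samples t test between the groups, with no adjustment for baseline.

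**The concern.** The sample size rests on a difference of about one SD. The text around it speaks of moderate detectability and moderate expected differences. A difference of one SD is not moderate on the usual reading, and the article gives no power figure for anything smaller. A reader would reasonably conclude that the trial is well placed to find a moderate difference, and would judge its results on that basis.

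The planning effect is also poorly known. It comes from 20 men and one of many primary measures, so it is weak support for expecting a difference of that size in the trial.

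**Working it through.** **Inputs.** From Sample size {14}: means 10.59 and 8.17; SDs 2.80 and 2.01; pilot n = 10 per group; α = 0.05; power 0.95; minimum N = 46; enrolled N = 60; dropout 15%. From Concealment mechanism {16b}: 1:1 allocation. From Statistical methods {20a}: unadjusted two-sample t test. Assumption: moderate means d = 0.5, with 0.4 to 0.7 shown as a range.

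**1. The plan's effect size.** Pooled SD = √[(2.80² + 2.01²)/2] = √[(7.840 + 4.040)/2] = 2.437. Difference = 10.59 − 8.17 = 2.42. d = 2.42/2.437 = 0.993, against 0.992 stated. It is reproduced to rounding.

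**2. The plan's sample size.** Power for the t test comes from the noncentral t distribution, with n₁ + n₂ − 2 degrees of freedom and noncentrality d·√[n₁n₂/(n₁ + n₂)]. At d = 0.992 and 23 per arm, power is 0.952 one-sided and 0.908 two-sided. So 46 is reproduced, but only one-sided; a two-sided test at 95% power needs 28 per arm, 56 in total. Because sidedness is not stated, both are carried below.

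**3. Precision of the pilot effect.** t = 0.993 × √(10 × 10/20) = 0.993 × 2.236 = 2.22 on 18 degrees of freedom. Inverting the noncentral t gives a 95% CI for d of about 0.05 to 1.91.

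**4. Completers.** 60 × 0.85 = 51, taken as 26 and 25.

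**5. Power for smaller differences.** With 26 and 25 men, √[26 × 25/51] = 3.570, so the noncentrality at d = 0.5 is 0.5 × 3.570 = 1.785 on 49 degrees of freedom.

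| True difference (SD) | 51 men, two-sided | 51 men, one-sided | 60 men, two-sided | 60 men, one-sided |
|---|---|---|---|---|
| 0.4 | 0.288 | 0.406 | 0.332 | 0.455 |
| 0.5 | 0.417 | 0.546 | 0.478 | 0.606 |
| 0.6 | 0.556 | 0.680 | 0.628 | 0.743 |
| 0.7 | 0.688 | 0.794 | 0.760 | 0.850 |
| 0.992 | 0.935 | 0.968 | 0.965 | 0.984 |

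**6. Detectable difference.** Solving the same formula for d:

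| Men | Test | 80% power | 95% power |
|---|---|---|---|
| 51 | two-sided | 0.80 SD | 1.03 SD |
| 51 | one-sided | 0.71 SD | 0.94 SD |
| 60 | two-sided | 0.74 SD | 0.95 SD |
| 60 | one-sided | 0.65 SD | 0.86 SD |

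In degrees of VM pennation angle, 0.80 SD is 0.80 × 2.437 = about 2.0°.

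**The case against.** The strongest reply is linguistic. In the disputed phrase, the adverb qualifies how detectable the change is, and no effect size is named, so the section makes no explicit claim about 0.5 SD. That is fair: a reader might infer a numerical power claim that the words do not contain. The phrase is then uninformative rather than false, and it still sits beside a hypothesis of moderate differences that the calculation does not address.

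Second, 0.5 SD is an outside convention. This also stands, which is why a range is shown. At 0.7 SD with all 60 men and a one-sided test, power reaches 85%. At 0.5 SD, no combination of sidedness and retention reaches 80%.

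Third, the trial is well powered for its own planning effect: 93% two-sided with 51 men at d = 0.992. That is true, but it answers a different question from the one the hypothesis poses.

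Fourth, a baseline-adjusted analysis would be more sensitive. The protocol does not plan one and gives no correlation between the before and after measurements, so it cannot be credited with that gain.

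Two stronger readings are tempting and should be resisted. A reader might infer that the trial would miss a moderate difference more often than not. That holds two-sided at 0.5 SD, but not on the one-sided basis that reproduces 46 (55% or 61% power), nor two-sided at 0.6 SD (56% with 51 men). A reader might also infer that the plan invites a null result to be read as equivalence. Nothing in the document plans or suggests an equivalence conclusion; the stated hypothesis is a difference.

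**Conclusion.** The mismatch is real. The effect size of 0.992 is computed correctly, and 46 follows from it one-sided. The fault is that sensitivity and hypothesis are described as moderate when the design was sized on a much larger difference, known only to within about 0.05 to 1.91 SD.

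The headline power of 42% holds under three conditions together: moderate means 0.5 SD, the test is two-sided, and 51 men complete. Changing sidedness or retention moves it to between 48% and 61%, still short of 80% and far from the 95% used for planning. All figures assume the unadjusted t test with equal variances, and the conversion to degrees assumes the pilot SD. The point should be corrected, but it concerns a description of the design and does not show that the design is unusable.

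**What to change.** In Sample size {14}, delete the phrase about a moderately detectable change. In its place, state whether the test is one-sided or two-sided, and give the detectable difference for 51 evaluable men at a named power. For a two-sided test at α = 0.05 this is 0.80 SD (about 2.0° of VM pennation angle at the pilot SD) at 80% power and 1.03 SD at 95% power. Add that power for a 0.5 SD difference is about 42% two-sided.

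In the Discussion, either say what size of difference moderate denotes or reword the hypothesis so that it agrees with this sensitivity.

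The cost is a few sentences and a less favourable statement of what the trial can show. The sample size, procedures and analysis stay as they are; the trial should not be enlarged on this account.

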### Recruitment {15}

Volunteers will be recruited through posters published in the official newspapers in the Latakia City, as well as via social media. Recruitment will finish once the number of volunteers required is complete. There will be no paid incentives to participate in this study, but the researcher will be responsible for all transportation costs and things necessary for sports (shoes, uniforms, water bottles).

## Assignment of interventions: allocation

### Sequence generation {16a}

The random allocation sequence will be created in permuted blocks of four and six using random allocation software version 1.0.0 [47].

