**Methods:**

The study sample consists of 60 untrained but healthy men (50–60 years old), who will be randomly assigned (strata: age, activate) to two groups: football group (*n* = 30) and aerobic group (*n* = 30). The intervention will take place within 12 consecutive weeks, two times a week for 60 min each session. The football group will perform recreational football training as a large-sided game, whereas the aerobic group undergoes a running exercise. Both groups have the same external workload ranging between moderate and high exercise intensity. The outcome measure will be collected before and after the intervention period.

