### Eligibility criteria {10}

Inclusion criteria are as follows: (1) healthy adult male volunteers between the ages of 50 and 60 years old, (2) participants must be in good health as determined by screening medical history and physical examination, and (3) they must not suffer from any neuromuscular, cardiovascular, or psychiatric disorder. The International Physical Activity Questionnaire (IPAQ) will be used to measure health-related physical activity in populations. IPAQ has reasonable measurement properties for monitoring population levels of physical activity among 18–65 years old adults in diverse settings [15]. The questions are about the time you spent being physically active in the last 7 days. They include questions about activities you do at work, as part of your house and yard work, to get from place to place, and in your spare time for. The long, self-administered IPAQ questionnaire has acceptable validity [42].

Exclusion criteria are as follows: (1) participants who have a significant history of alcoholism or drug/chemical abuse within the last 2 years; (2) participants with positive results on tests for drugs of abuse or alcohol at screening and check-in; (3) history of unstable psychiatric disorder requiring medications or hospitalization within the previous 12 months; (4) history of a concurrent illness that required hospitalization within 14 days prior to day 1 of the study; (5) any condition that in the clinical judgment of the investigator would make the subject unsuitable for participation; (6) participants who have had a clinically significant illness within 4 weeks prior to day 1; (7) history or current evidence of clinically significant hepatic, renal, cardiovascular (i.e., deep venous thrombosis, pulmonary embolism), psychological, pulmonary, metabolic, endocrine, neurologic (i.e., transient ischemic attack or stroke within the past 6 months), infectious, gastrointestinal (i.e., any condition which may affect drug absorption), hematologic, and oncologic disease, retinopathy, or other medical disorders; (8) history of unexplained syncope; and (9) participants who, in the opinion of the investigator, should not participate in the study.

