### Concealment mechanism {16b}

Allocation concealment will be achieved using sequentially numbered, opaque sealed envelopes [17]. Participants will be assigned in two intervention groups: a football group and aerobic group in a 1:1 ratio. Allocation concealment will be ensured. The randomization code will not release until the participants have been recruited into the trial, which takes place after all baseline measurements have been completed.

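### The abstract names age and activity as randomisation strata, but the allocation sections name none and the planned t test leaves them out; the two should be reconciled and the test replaced by a baseline- and strata-adjusted model (minor).

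*Protocol article*

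**What the plan says.** Abstract, Methods: the 60 men are those "who will be randomly assigned (strata: age, activate) to two groups". This is the only mention of strata in the article. No levels or cut-points are given.

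Sequence generation {16a}: "The random allocation sequence will be created in permuted blocks of four and six using random allocation software". No strata are named. Concealment mechanism {16b} adds sealed envelopes and "a football group and aerobic group in a 1:1 ratio". Implementation {16c} describes who requests and handles the randomisation. Neither mentions strata, nor do Trial design {8} and Study setting {9}.

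Eligibility criteria {10}: "The International Physical Activity Questionnaire (IPAQ) will be used to measure health-related physical activity in populations". The questionnaire is a possible source for an activity stratum, but it is not linked to allocation.

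Statistical methods {20a}: paired t tests within each arm, and an independent-samples t test that "will be used to compare the mean between the football and aerobic groups before and after the intervention". The sections on additional analyses {20b} and on missing data {20c} add no covariate.

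Sample size {14}: an effect size of 0.992 from a pilot of 10 men per group, and "The α level was 0.05, and the power was 0.95".

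**The concern.** A reader cannot tell from the article whether the block sequence is run within age-by-activity strata. If it is, the named analysis does not reflect the design. Stratified allocation makes the arms alike on the strata, so the difference in means varies less from trial to trial. The t test nevertheless estimates its standard error as if stratum differences were random noise between the arms. The interval is then wider than the design warrants, and the test rejects less often than its nominal level. If allocation is not stratified, the abstract credits the trial with a property it lacks. What is at stake is precision and accurate reporting, not false-positive control.

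**Working it through.** **1. The text side by side.** The abstract asserts strata. The sequence section gives block sizes and software only. Permuted blocks are the usual way to randomise within strata, so the two statements can both be true. The t test, by contrast, is positively named and contains neither strata nor baseline.

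**2. The plan's own figure.** From the pilot in Sample size {14}, d = (10.59 − 8.17) / √((2.80² + 2.01²)/2) = 0.993, in line with the stated 0.992. A two-sample t test with d = 0.992, α = 0.05 and power 0.95 needs 23 per arm one-sided (total 46, as stated) and 28 per arm two-sided (total 56). The calculation contains no strata, which matches the planned t test. Its one-sided basis is a separate matter. It is used here only for the planning effect, 0.992.

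**3. Approximate effect on the t test if allocation is stratified.** Let R² be the share of outcome variance explained by the strata, and let σ be the total SD. With the strata balanced, the true standard error of the difference is about σ√((1 − R²)·4/N), while the t test estimates about σ√(4/N). The real type I error is therefore about 2Φ(−1.96/√(1 − R²)):

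- R² = 0: 1.96/1 = 1.96, giving 5.0%
- R² = 0.10: 1.96/√0.9 = 2.07, giving 3.9%
- R² = 0.20: 1.96/√0.8 = 2.19, giving 2.8%
- R² = 0.30: 1.96/√0.7 = 2.34, giving 1.9%

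**4. Simulation.** From the documents: 60 men, 1:1, blocks of 4 and 6. Assumed: blocks run within four strata (two binary factors, levels equally likely), two-sided 0.05, R² as shown, and the 0.5 SD effect. There were 4000 runs per cell. The adjusted model contains arm and the two factors, without a baseline value.

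| R² | Type I error, t test / adjusted | Power at 0.5 SD, t test / adjusted | Power at 0.992, t test / adjusted |
|---|---|---|---|
| 0 | 5.4% / 5.5% | 48% / 47% | not run |
| 0.05 | not run | not run | 97.0% / 97.4% |
| 0.10 | 3.9% / 5.1% | 48% / 52% | 97.3% / 98.2% |
| 0.20 | 3.0% / 5.1% | 47% / 56% | 97.5% / 98.7% |
| 0.30 | 1.9% / 4.6% | 46% / 62% | 98.0% / 99.3% |

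The simulation standard error is about √(0.05 × 0.95/4000) = 0.3 points for the type I errors and √(0.48 × 0.52/4000) = 0.8 points for power near 48%. The 5.4% and 5.5% in the first row are thus compatible with 5%.

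The loss at 0.5 SD is about 0, 4, 9 and 16 points for R² of 0, 0.10, 0.20 and 0.30. At 0.992 it is 0.4, 0.9, 1.2 and 1.3 points for R² of 0.05 to 0.30, so at most about 1.4 allowing for rounding.

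**5. If allocation is not stratified.** In the same set-up with a single blocked list, the type I error of the t test stayed between 4.8% and 5.4% for R² from 0 to 0.5. It holds its nominal level.

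**The case against.** The best defence is that the sequence section is merely silent. A condensed article may leave stratum cut-points and per-stratum lists to the full protocol, and blocks of four and six fit a stratified scheme. That stands. A reader might infer that the article describes two different randomisations, or that the list is a single unstratified one; nothing in the allocation sections says so.

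Second, the loss may be slight. The documents do not say how strongly age or activity predicts the outcomes, and both are restricted by eligibility: men of 50 to 60, all untrained. With weak strata almost nothing is lost, and at the planning effect the loss is small throughout. This stands too. It is tempting to say that ignoring the strata costs the equivalent of 25% more men, since 1/(1 − 0.20) − 1 = 0.25, but that rests wholly on an assumed 20% of variance explained. Against this, the Discussion expects only moderate differences between the groups, so effects smaller than 0.992 are relevant, and there the loss can be material.

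Third, the simulation compares strata with no covariate at all. Once the baseline value is in the model, the strata may add less. That is fair, and it is why the fix puts the baseline value in the model in either case.

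What the defence does not remove is that the abstract states a design feature which the operative allocation sections do not carry, and that the named test ignores it.

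**Conclusion.** The point holds as a minor one. The abstract and the allocation sections must be made to agree, and the between-group test should use the factors the trial says it randomises by, together with the baseline it already measures. If allocation is stratified, the t test is conservative: type I error falls from about 5% to about 2% as the variance explained rises from 0% to 30%. The power loss over that range is about 0 to 16 points at 0.5 SD. At 0.992 it is at most about 1.4 points over 5% to 30% explained. These figures assume four equally likely strata, two-sided testing and the R² values shown; the documents supply none of these.

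A reader might infer that the planned test threatens the validity of the result. It does not: the estimate is not biased by omitting the strata, and false positives are not inflated on either reading of the allocation.

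**What to change.** 1. Make the abstract and Sequence generation {16a} agree on whether allocation is stratified by age and activity, and correct the word printed as *activate*.
2. In Statistical methods {20a}, replace the post-intervention independent-samples t test with a linear model (ANCOVA) of the post-intervention value on arm, baseline value and the stratification factors.
3. If allocation was not stratified, remove the strata from the abstract and keep the baseline-adjusted model. Adjusting for age and activity is then optional.

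The cost is a few words and one linear-model command in SPSS. Age and the activity questionnaire are already part of screening, and the outcomes are already measured before the intervention, so no new data are needed.
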